## Objectives

The ECHO study has four primary objectives described below:The primary obstetric objective is to establish whether infants born to women who vape are at a higher or lower risk of adverse outcomes in pregnancy compared to infants of combustible cigarette smokers and non-smokers.The primary neonatal objective is to assess anthropomorphic variation, if any, in newborn babies born to vapers in comparison to smokers and controls. The primary paediatric objective is to establish whether parent-reported and doctor-confirmed wheeze and/or asthma occurs more frequently in children exposed to vaping in utero compared with children of combustible cigarette smokers and non-smokers.The primary neurocognitive objective is to assess if there are significant differences in neurocognitive outcomes between the infants of a women who vape compared to infants of women who used combustible cigarette smokers and non-smokers.Globally, we aim to correlate, obstetric, neonatal, pulmonary, growth and neurocognitive differences, if any, to quantitative levels of cotinine excreted in maternal urine at in the third trimester.

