## Outcomes

### Primary outcomes

The primary outcomes outlined in Table 2 have informed the sample size calculation. As the outcomes for the postnatal psychological assessments are exploratory, we have used a pragmatic sample target of 150.

**Table 2. Tab2:** Primary outcomes

Primary outcomes		
Obstetrics/neonatal	Paediatrics	Psychology
• Preterm birth • Low birth weight	• Doctor-diagnosed wheeze	• Neonatal Behavioural Assessment Scale • Bayley’s Infant and Toddler Development (*n*=150)

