**Table Taba:** 

Women who vape during pregnancy will be more likely have a preterm birth and that their infants will have a lower birth weight (LBW), lower neuro-behavioural scores and increased respiratory symptoms when compared with non-smokers.
Women who vape during pregnancy will be less likely to have a preterm birth and their infants will have a higher birth weight, higher neuro-behavioural scores, and fewer respiratory symptoms than when compared with tobacco smokers.

The best available data suggest a prevalence of smoking rate during pregnancy in Ireland is between 9 and 10% [44], whilst the current expected rate of vaping during pregnancy is approximately 5% [45]. The cumulative live birth rates in the three maternity hospitals in Dublin in 2023 were: The Coombe Hospital—6974, The Rotunda Hospital—8442, and the National Maternity Hospital—6880, which will give a projected denominator of approximately 22,000 total live births. The incidence of vaping during pregnancy in the Coombe is 5% [34, 46]; projected to the other three hospitals gives approximately 750–1250 vapers per annum. The calculations in Table 3 give the magnitude of a detectable association with (2-year) prevalence of each condition (odds ratios) or mean differences that are detectable at a power of 80%, with a type I error rate of 0.05. These assume use of simple uncorrected Chi-square test or *t* tests. Detectable effect sizes are presented assuming a range of sample sizes to illustrate how power is maintained under a range of recruitment scenarios. We plan to collect three equally sized groups—non-smokers, smokers, and vapers

**Table 3 Tab3:** Sample size calculation

Sample size (per group)	Baseline incidence		
	10% (wheeze)	6.2% (preterm birth)	5% (low birth weight)
	Detectable odds ratios:		
100	3.00	3.62	3.19
200	2.25	2.63	2.26
300	1.96	2.24	1.91
**400**	**1.80**	**2.04**	**1.74**

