Whilst robust data on the effect of vaping during pregnancy on women and infants are lacking, the effects of smoking are well characterised on neonatal anthropometric measurements. Asthma or wheeze has an incidence of approximately 10% within the first 3 years of life [47]. LBW occurs at a frequency of about 5% [48]. PTB occurs in approximately 6.2% of births in Ireland [49]. Maternal smoking has been shown to increase risk of asthma or wheeze in childhood with an odds ratio of 1.8 (95% CI 1.35–2.53). Smoking has also been shown to increase incidence of LBW with an odds ratio of 1.75 (95% CI 1.42–2.10). The odds ratio for PTB conferred by smoking is 1.27 (95% CI 1.20–1.33).

Data on neurocognitive outcomes is lacking; neurocognitive outcomes between groups can be expressed as standardised mean differences (SMD). Table 4 gives indicative detectable differences for each sample size. For reference, caregiver depression has been as a risk factor on the NBAS with a SMD of 0.28 [50] and smoking demonstrated an association of the order of SMD = 0.2–0.4 for executive function including inhibition and self-control [51].

**Table 4 Tab4:** Indicative detectable differences per sample size

Sample size (per group)	Standardised mean difference
100	0.40
200	0.28
300	0.23
**400**	**0.20**

Therefore, we propose to recruit 1200 participants (400 smokers, 400 vapers and 400 non-smoker, non-vaper controls) to generate adequate power and precision to answer our research questions.

In the case that key measurements are missing at rates in excess of 5%, multiple imputation procedures will be considered. We anticipate the likelihood of missing data is small given the standard procedures in place to manage the study centrally.

Case report form (CRF) data entry into REDCap will include extensive data validation checks. Missing data will be monitored, and strategies will be developed to minimise its occurrence. Central statistical data monitoring will summarise missing or inconsistent data periodically. The study workbook will be approved by the chief investigator and validations will also be made that will cross-check the study workbook with the ECHO study electronic CRF.

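### The primary paediatric endpoint is defined in two ways, and the sizing takes its 10% event rate from a third event and a longer window

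*Protocol article*

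**What the plan says.** The Objectives section sets out, as the primary paediatric aim, to "establish whether parent-reported and doctor-confirmed wheeze and/or asthma occurs more frequently in children exposed to vaping in utero". Table 2, under Primary outcomes, lists one paediatric entry: "Doctor-diagnosed wheeze". The text above that table ties it to the sizing: "The primary outcomes outlined in Table 2 have informed the sample size calculation".

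Under Power calculations and rationale, Table 3 heads its 10% column with wheeze alone, and the text introducing the table speaks of a 2-year prevalence. The paragraph that justifies the figure says something else: "Asthma or wheeze has an incidence of approximately 10% within the first 3 years of life". The reference effect is also for the combined event: "Maternal smoking has been shown to increase risk of asthma or wheeze in childhood with an odds ratio of 1.8". The hypotheses in the same section use a looser phrase, "increased respiratory symptoms when compared with non-smokers".

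Follow-up ends at 2 years: questionnaires at 6 months, 1 year and 2 years, and infant assessments at 12 and 24 months. Episodes of wheeze at 6, 12 and 24 months are listed under Paediatric secondary outcomes.

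**The concern.** A primary endpoint has to let two analysts with the same data count the same cases. Here the objective and the outcome table differ on two points: whether asthma counts, and whether a parent's report is required in addition to the doctor's. Both wordings stand in the current text as the primary paediatric endpoint, so this is a contradiction and not a detail left to a fuller document.

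Two things are at stake. The comparison of vapers with smokers and with controls could come out differently according to which wording is applied. And the 80% power quoted for this endpoint belongs to an event rate that the plan attaches to a different event over a longer period than the study observes.

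**Working it through.** **Side by side**

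| Place | Event | Source of the report | Window |
|---|---|---|---|
| Objectives | wheeze and/or asthma | parent and doctor | none given |
| Table 2 | wheeze | doctor | none given |
| Table 3 and its introduction | wheeze | none given | 2 years |
| Text giving the 10% | asthma or wheeze | none given | first 3 years |

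**Children classified differently**

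- Asthma reported by the parent and confirmed by a doctor, with no wheeze diagnosis: a case under the objective, a non-case under Table 2.
- Wheeze diagnosed by a doctor but not reported by the parent: a case under Table 2, a non-case under the objective.

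The documents do not allow either group to be counted.

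**Reproducing the plan's figure**

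Inputs from Power calculations and rationale: control rate p1 = 0.10, n = 400 per group, equal groups, uncorrected chi-square test, with effects "detectable at a power of 80%, with a type I error rate of 0.05". Sidedness is not stated; two-sided reproduces the table.

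Formulas:

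- p2 = OR × p1 / (1 − p1 + OR × p1)
- s0 = √[2 × p̄(1 − p̄)/n], with p̄ the mean of p1 and p2
- s1 = √[(p1(1 − p1) + p2(1 − p2))/n]
- power = Φ[(p2 − p1 − 1.96 × s0)/s1]

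At OR 1.80:

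- p2 = 0.18/1.08 = 0.1667, so the difference is 0.0667
- s0 = 0.02404 and s1 = 0.02392
- power = Φ[(0.0667 − 0.0471)/0.02392] = Φ(0.8175) = 79.3%

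Solving for 80% power at 100, 200, 300 and 400 per group gives odds ratios of 2.99, 2.25, 1.96 and 1.81, against 3.00, 2.25, 1.96 and 1.80 in Table 3. The arithmetic for this column is sound.

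**Sensitivity to the event rate**

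The documents give no separate rate for either definition, so every rate below except 10% is an assumption (400 per group):

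| Control rate | Power at OR 1.8 | OR detectable at 80% power |
|---|---|---|
| 5% | 53.6% | 2.17 |
| 7% | 66.4% | 1.97 |
| 8% | 71.5% | 1.91 |
| 10% (plan) | 79.3% | 1.81 |
| 12% | 84.9% | 1.74 |
| 15% | 90.3% | 1.67 |

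For 7%: p2 = 0.126/1.056 = 0.1193, difference 0.0493, s0 = 0.02070, s1 = 0.02063, and Φ(0.424) = 66.4%.

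**The case against.** The strongest reply is that both wordings need a doctor and that most cases may be common to both, so the choice might hardly move the result. That stands as a limit on the claim: the documents show that the definitions can give different results, not that they do. The study is also registered, and a full protocol or analysis plan may already hold an operational definition. That cannot be ruled out, so deliberate choice of a definition after the results are seen is not established. It does not remove a conflict that this document states itself.

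A reader might infer several stronger points that the documents do not support:

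- *That the hypotheses add a rival endpoint, so that a child who wheezes at home and never sees a doctor exposes the contradiction.* That child is a non-case under both the objective and Table 2. The phrase on respiratory symptoms sits in a directional summary and need not be a case definition.
- *That diagnosing clinicians know the mother's smoking status and label accordingly.* Nothing is said about what they know.
- *That unequal attendance at doctors measures the size of this problem.* It could bias any endpoint that depends on a doctor, including both wordings here. It is a separate issue, and choosing between the two wordings would not remove it.
- *That the study is underpowered for wheeze.* The rates of 7% and 15% are illustrations. The power could move either way.

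**Conclusion.** The point holds as an internal contradiction in a declared primary outcome. The objective and Table 2 define different events, and the sizing borrows its 10% and its odds ratio of 1.8 from the combined event, with the 10% over 3 years, while labelling the column as wheeze beside a 2-year prevalence. The calculation itself is correct for a 10% rate; the unsettled part is which event and window that rate describes.

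The effect on the primary comparison cannot be sized from the documents. The effect on power is conditional: with 400 per group and an odds ratio of 1.8, it is about 66% if the chosen definition gives an assumed 7% by 24 months, 79.3% at 10%, and about 90% at an assumed 15%. These figures rest on a two-sided uncorrected test and full follow-up of all 400 in each group.

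**What to change.** Before outcome data are analysed:

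1. Choose one case definition, stating whether asthma counts and whether a parent's report is required as well as the doctor's.
2. Choose one window, by 24 months, which matches the end of follow-up.
3. Write both identically in the Objectives, Table 2, the hypotheses and the sizing text, and label Table 3 to match.
4. Make the baseline rate and the detectable odds ratio refer to that definition and window. If no source gives such a rate, say so and show a range like the one above.
5. Report parent-reported wheeze from the 6-, 12- and 24-month contacts next to the primary result, as a secondary check on ascertainment.

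The cost is wording in a few places, a restated row or range in the sizing, and one extra table from data the plan already intends to collect. The downside is that the event rate for the chosen definition may be below 10%, in which case the stated power will be lower.

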### Obstetric secondary outcomes

Trends in smoking cessation and crossover from smoking to vaping and from vaping to non-smoking/non-vaping/smoking.BCO at screening, 20 weeks, third trimester, and postnatally.Quantitative urine cotinine assay in the third trimester.Estimated fetal weight (EFW)—using the Hadlock formula [41]—fetal and maternal dopplers at 20 weeks and 32–34+6 (maternal: uterine artery Doppler, fetal: umbilical artery, middle cerebral artery, cerebroplacental ratio).Incidence of small for gestational age (SGA) defined as EFW and/or AC less than the 10th centile for gestational age on ultrasound at any gestation after study entry.Diagnosis of congenital malformation.Birth centile [42].Blood pressure measurement at screening, 20 weeks and third trimester, and postnatally.Incidence of essential hypertension—high blood pressure at booking defined at a BP 140/90 mmHg.Incidence of diagnosis of pregnancy-induced hypertension and incidence pre-eclampsia [43].Incidence of pre-labour premature rupture of membranes (PPROM).Incidence of anaemia, defined as a haemoglobin level of less than 10g/dL at booking, 28 weeks or any other time point in the antenatal period.Maternal history of abnormal cervical screening cytology or cervical surgery.Indication for and incidence of induction of labour.Mode of delivery.Delivery complications.Incidence of postnatal caesarean, episiotomy or perineal wound infection requiring antibiotics.Edinburgh Postnatal Depression Scores prior to discharge.Incidence of venous thromboembolic (VTE) disease—new onset deep venous thrombosis or pulmonary embolus.Unscheduled admission to hospital.Admission to high dependency unit (HDU) or inter-hospital transfer to intensive care unit.

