**Methods:**

Pregnant women attending three, large, standalone, urban, university, maternity units in Dublin, Ireland, will be invited to take part in this prospective, multicentre, observational cohort. Smoking and vaping patterns will be assessed using digital patient questionnaires. Objective assessment of breath carbon monoxide and urine cotinine levels will accurately determine exposure status at pre-specified timepoints. A third trimester ultrasound will assess growth and fetal dopplers across all groups. Postnatally, infants will undergo anthropometric measurements and developmental checks. A subgroup of 150 randomly selected infants will be assessed with the Bayley’s Scales of Infant and Toddler Development.

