### Population

This prospective, multicentre, observational cohort will focus on women pregnant with a singleton fetus who self-report vaping, cigarette smoking, vaping and cigarettes smoking, or no exposure (controls). The obstetric portion of the study operates from three recruitment sites; The Coombe Hospital, The Rotunda Hospital, and the National Maternity Hospital—these standalone maternity units, based in Dublin, Ireland’s capital city, cumulatively deliver approximately 22,000 women annually [31–34].

Smoking and vaping patterns will be assessed using a combination of digital validated patient questionnaires administered at set timepoints throughout pregnancy, in addition to objective assessment of exhaled breath carbon monoxide (BCO) assessed by point of care exhaled carbon monoxide breathalysers (Bedfont’s ‘Smokerlyzer’® device) at each antenatal study visit. Nicotine levels will be assessed using quantitative urinary cotinine, analysed by Eurofins Biomnis enzyme immunoassay.

Women are recruited prior to 24-week gestation after being directly asked about smoking and vaping status in a structured fashion at their booking visit; if they fulfil the eligibility criteria, they are then invited to partake in the study as either a vaper, a smoker, a smoker/vaper or a control (Table 1.).

**Table 1 Tab1:** Exposure status

Vaper	Vaper/smoker	Smoker	Control
• Reports vape use • BCO ≤4 ppm	• Reports dual use • BCO ≥ 5 ppm	• Reports cigarette smoking • BCO ≥ 5 ppm	• Denies cigarette smoking or vaping • BCO ≤4 ppm

A BCO measurement of ≥ 5 parts per million (ppm) was selected to define active smoking, in keeping with Irish National Clinical Guidance. Selection of BCO ≥ 5 ppm as a cutoff confers a sensitivity of 0.9 and specificity of 0.92 [35]. This is an important consideration in accurately classifying both smokers and smoker/vapers in addition to self-reported exposure status.

After screening, demographic and biometric data points are gathered, and a series of questionnaires are administered digitally as per the schedule outlined below:

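### SGA is counted on any scan after entry, so its group comparison is open to detection bias if scan frequency differs by exposure

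*Protocol article*

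**What the plan says.** All references are to the protocol article.

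- **Definition.** Under Obstetric secondary outcomes, SGA is an estimated fetal weight and/or abdominal circumference "less than the 10th centile for gestational age on ultrasound at any gestation after study entry". The rule names no visit, does not limit itself to study scans and sets no number of scans.
- **Scheduled scans.** The same list places estimated fetal weight, with "fetal and maternal dopplers at 20 weeks and 32–34+6" weeks. The abstract's Methods paragraph adds: "A third trimester ultrasound will assess growth and fetal dopplers across all groups".
- **Entry.** Under Population: "Women are recruited prior to 24-week gestation after being directly asked about smoking and vaping status", which happens in a structured way at the booking visit. Entry can therefore fall before or after the 20-week scan.
- **Other growth measures.** "Birth centile [42]" is a separate secondary outcome, and low birth weight is a primary outcome (Table 2).
- **Group sizes.** The target is "400 smokers, 400 vapers and 400 non-smoker, non-vaper controls".
- **Analysis.** The section on sample size and planned analyses provides in general terms for potential confounders to enter the models. Nothing in the article standardises the number or timing of scans that feed the SGA outcome.

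**The concern.** The definition is an ever-flagged rule: one scan below the threshold makes a case, and no later scan can reverse it. Each further scan adds a chance of being counted. A rule of this kind compares groups fairly only if they are scanned equally often.

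There is a plausible way for scanning to be unequal. Smoking and vaping status is asked about directly at booking, and the article's Background lists SGA among the harms of smoking. A clinician who knows the exposure could request more growth scans, and as the definition is worded any of these would count. A difference in SGA could then reflect how often women were scanned and not how their fetuses grew.

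The Discussion treats SGA in vapers as an open question: registry studies found more of it, and an earlier prospective cohort at one of the study hospitals found no difference. The Discussion faults the registry data for recall and selection bias, so an avoidable route to detection bias on the same outcome is worth closing.

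**Working it through.** The article gives no SGA rate, effect size or power, so there is no stated figure to reproduce. The check is of the mechanism and its likely scale.

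**Inputs from the article:** the 10th-centile cut; scheduled scans at 20 and 32–34+6 weeks; entry before 24 weeks; 400 women per group.

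**Assumed inputs, not in the article:** each scan flags 10% of fetuses; growth is identical in all groups; scan results are equally correlated normal scores, with correlation 0.3 to 0.9; the scan counts and entry-time mixes below. The and/or rule on weight and circumference would push the per-scan rate above 10%; this is ignored.

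**Step 1: chance of at least one flag in k scans.** This is the probability that at least one of k correlated standard normal scores falls below −1.2816.

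| Correlation | 1 scan | 2 scans | 3 scans |
|---|---|---|---|
| 0.9 | 10.0% | 13.1% | 15.0% |
| 0.7 | 10.0% | 15.3% | 19.0% |
| 0.5 | 10.0% | 16.8% | 21.8% |
| 0.3 | 10.0% | 17.8% | 24.2% |

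**Step 2: unequal scan frequency, correlation 0.7.** Every woman has one counted scan; 30% of group A and 60% of group B have one more.

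- A: 0.100 + 0.3 × (0.153 − 0.100) = 0.116
- B: 0.100 + 0.6 × (0.153 − 0.100) = 0.132
- Spurious odds ratio: (0.132/0.868) / (0.116/0.884) ≈ 1.16

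At 400 per group, a two-sided 5% test would reject in about 10% of studies. Over correlations 0.9 to 0.3 the odds ratio runs from 1.10 to 1.22.

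If every woman instead starts from both scheduled scans, the same 30% and 60% give:

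- A: 0.153 + 0.3 × (0.190 − 0.153) = 0.164
- B: 0.153 + 0.6 × (0.190 − 0.153) = 0.175
- Spurious odds ratio: (0.175/0.825) / (0.164/0.836) ≈ 1.08 (range 1.05 to 1.12)

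**Step 3: unequal entry time, correlation 0.7.** Suppose 90% of one group and 60% of another enter before the 20-week scan, with no extra scans.

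- 0.9 × 0.153 + 0.1 × 0.100 = 0.148
- 0.6 × 0.153 + 0.4 × 0.100 = 0.132
- Spurious odds ratio: (0.148/0.852) / (0.132/0.868) ≈ 1.14 (range 1.09 to 1.19)

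The higher rate goes to whichever group enters earlier.

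**Step 4: equal scanning.** If scan counts and entry times have the same distribution in every group, the expected rates are equal and there is no differential bias. The same holds by construction for a single fixed time point: each woman has one chance, whatever her other scans.

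**The case against.** The strongest reply is that repeated looks bias a group comparison only if their number differs by exposure, and the article never says that it does. That stands. A reader might infer that SGA will be inflated in smokers and vapers; the article supports only that it could be.

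A second tempting inference is that the recruitment window itself makes the groups unequal. It does not. It makes women differ, under one rule for all groups, and nothing ties entry before or after 20 weeks to exposure. Recruitment is linked to the booking visit, and other measures are listed at screening and then at 20 weeks, so entry before 20 weeks looks like the usual path. If exposed women entered later, this route would lower their SGA count.

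A third is a large effect. Odds ratios of 1.4 to 2.5 do come out of the model for correlations of 0.85 to 0.5, but only if every woman in one group has two or three counted scans and every woman in the other exactly one. Both scheduled scans apply to all groups, so that contrast is not realistic here.

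It is also fair to say that ever-diagnosed SGA is a legitimate incidence outcome, that fixed-time growth measures are already collected, and that sensitivity analyses may sit in a document not shown. These points lower the severity. They do not remove the issue, because the definition is stated in the article and is the one that would be compared. Nor does general confounder adjustment settle it: scan count is not a baseline factor. It can follow from both exposure and suspected poor growth, so conditioning on it may add bias.

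Finally, a comparison on the late scan alone would lose women delivered before it, and the study hypothesises that preterm birth differs by exposure. That stands, and the fix has to deal with it.

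**Conclusion.** The point holds as an avoidable weakness in a secondary outcome. The any-scan rule makes the probability of being classed SGA depend on how often a woman is scanned, and the group comparison is open to detection bias if that frequency differs by exposure. Entry before or after the 20-week scan is a weaker route, of unknown direction.

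The size in this study is unknown. The odds ratio of about 1.16 is an illustration that rests on an assumed 60% against 30% split, 10% flagged per scan, correlation 0.7 and one counted scan as the starting point; it falls to about 1.08 from two. The article does not support a claim that bias is present or that it runs against the exposed groups.

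Severity is minor: SGA is neither a primary outcome nor a basis for the sample size, every group has the third-trimester scan, and birth centile is collected separately.

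**What to change.** Amend the outcome definition in three parts:

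1. Make the between-group SGA comparison on the scheduled 32–34+6 week scan, using the existing criterion on estimated weight and/or abdominal circumference.
2. Pair it with birth centile below the 10th for all births, so that pregnancies delivered before that scan are still counted. Report by group how many women had no scheduled late scan.
3. Keep SGA on any scan as a descriptive outcome, reported with the number of scans per woman and gestation at entry by group.

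The cost is a few sentences and a record of how many scans each woman had; no new scan or measurement is needed. The downside is that fetuses flagged only on an unscheduled scan leave the main antenatal count, although they still appear in the descriptive one and, if small at birth, in the birth-centile comparison.

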## Background

Combustible cigarette smoking is the foremost modifiable risk factor for adverse pregnancy outcomes [2]; therefore, encouraging women to stop smoking in pregnancy is a key public health priority [3]. Combustible cigarette smoking during pregnancy is associated with an increased risk of fetal anomaly [4], small for gestational age and stillbirth, preterm birth, low birth weight [5], placental abruption, sudden infant death syndrome [6], respiratory morbidity in the neonatal period [7], asthma and longer term neurodevelopmental delay [8]. Increasingly, it is accepted that intrauterine growth and development are strong determinants of health, not only in the neonatal period, but also impact on childhood and adult health outcomes [9, 10]. Pregnancy can be a motivator for smoking cessation, with quit attempts higher than at any other time in a woman’s life [11]; smoking cessation prior to or during the first trimester of pregnancy significantly reduces the risk of preterm birth [8] and impacts positively on birthweight [12].

Nicotine replacement therapy (NRT) in the form of patches, inhalers, lozenges etc., has been prescribed for pregnant women seeking pharmacological support to stop smoking for decades; it accepted to be significantly less harmful to the fetus than continuing to smoke combustible tobacco cigarettes [13, 14].

Electronic cigarettes (E-cigarettes) or ‘vapes’ are viewed as a reasonable alternative to combustible cigarette smoking by some women and are now endorsed by some health policy makers in the United Kingdom to support women to stop cigarette smoking in pregnancy [15]. However, there is a paucity of high-quality, prospective data assessing the impact of electronic cigarettes on pregnancy, neonatal, and infant outcomes. In the following protocol, registered with ClincialTrials.gov (NCT06297005), we outline a multicentre, prospective, observational cohort study of pregnancies exposed to vaping to address this research gap.

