### Exclusion criteria

Twins or higher order multiplesLate bookers—defined as booking after 24+0 weeks’ gestational ageFetus or infant diagnosed with a major congenital abnormality requiring immediate admission to NICU +/- outward transfer for surgery, chromosomal abnormalitiesAny inherited disorder of metabolism or cystic fibrosis on Guthrie cardHistory of significant maternal medical disorderHistory of significant maternal psychiatric disorder, e.g. delusional or psychotic disorders, use of >1 psychotropic drugs for treatmentSerious co-morbid addiction issues, e.g. opiate abuseSevere intellectual disability or lack of capacity

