### Secondary neonatal outcomes

APGAR scores at 1 and 5 minutes.Brazelton’s Neonatal Behavioural Assessment Scale (NBAS).Umbilical artery blood gas (if available).Admission to neonatal intensive care (NICU) or special care baby unit (SCBU).Incidence of neonatal hypoglycaemia as per local guidelines.Incidence of neonatal jaundice requiring phototherapy.Mode and type of infant feeding.Neonatal anthropometric measurements (weight in grams, length, head, chest and waist circumference in centimetres).A subgroup of 150 infants will have PEAPOD assessment. The PEAPOD is a specialised scale that both weighs a baby and uses air displacement plethysmography to determine the baby’s body volume. These measurements allow us to calculate the baby’s density and estimate the baby’s body fat and lean body mass [41].

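### Part of the congenital malformation outcome is also a reason for exclusion after enrolment, so an exposure effect on that severe class cannot be seen

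*Protocol article*

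**What the plan says.** Under Obstetric secondary outcomes, the protocol article lists "Diagnosis of congenital malformation". It sets no limit by severity, type or time of diagnosis. Under Secondary neonatal outcomes it lists admission to a neonatal intensive care or special care baby unit.

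The Exclusion criteria remove a fetus or "infant diagnosed with a major congenital abnormality requiring immediate admission to NICU", with or without transfer out for surgery, and chromosomal abnormalities. The next criterion removes infants whose newborn screening card shows an inherited metabolic disorder or cystic fibrosis.

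On timing, the Population section says: "Women are recruited prior to 24-week gestation". On relevance, the Background says: "Combustible cigarette smoking during pregnancy is associated with an increased risk of fetal anomaly". Smokers are one of the three comparison groups. No section says whether a pregnancy excluded under these criteria still counts for the malformation outcome, or is dropped only from infant follow-up.

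**The concern.** The same event is an outcome in one section and a ground for removal in another. If it were known before entry, this would be an ordinary restriction of the study population. But a diagnosis in an infant, a need for immediate NICU care and a newborn screening result can be established only after birth, which is after enrolment and after exposure. Applied as written, the criterion selects on a possible consequence of exposure.

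Two results are at stake. The malformation comparison would lack its most severe class, so a finding of no difference would not cover those cases. The NICU/SCBU comparison would lose infants who are admissions by definition. The article expects its findings to inform guidelines on vaping and smoking in pregnancy, and a reader could take a malformation result to include the severe cases.

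**Working it through.** **Text comparison.** The outcome is any malformation. The exclusion covers (a) major abnormalities needing immediate NICU admission and (b) chromosomal abnormalities. Major malformations without immediate NICU need, and minor ones, stay countable. The outcome therefore loses part of its upper end and keeps the rest. Class (a) also lies wholly inside the NICU/SCBU outcome.

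**Size.** The plan has no malformation figure to reproduce. Only the group size comes from the article (Power calculations and rationale): "400 smokers, 400 vapers and 400 non-smoker, non-vaper controls". The rates below are assumptions.

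Let s be the control risk of an excluded-class malformation and m the control risk of any other. Let Rs and Rm be the risk ratios of exposure on each.

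- All cases counted: RR = (Rs·s + Rm·m) / (s + m)
- After exclusion: RR = Rm·(1 − s) / (1 − Rs·s)

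After exclusion, Rs survives only in a denominator close to 1, so the data carry almost no information on it.

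Assume 12 malformations in 400 controls (3%), 6 of them in the excluded class, so s = m = 0.015.

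| Assumed effect | Cases, exposed vs control | RR, all cases | After exclusion | RR |
|---|---|---|---|---|
| Excluded class doubled, others unchanged | 18 vs 12 | 1.50 | 6/388 vs 6/394 | 1.02 |
| Excluded class ×2, others ×1.5 | 21 vs 12 | 1.75 | 9/388 vs 6/394 | 1.52 |
| All malformations doubled | 24 vs 12 | 2.00 | 12/388 vs 6/394 | 2.03 |

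In the last row the ratio is preserved but the absolute excess is roughly halved: 24/400 − 12/400 = 3.0 percentage points, against 12/388 − 6/394 = 1.6.

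Range when the effect is confined to the excluded class:

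- Total rate 2–3%, excluded share 30–70%, Rs 1.5–2.0: RRs of 1.15–1.70 become 1.00–1.02.
- Total rate 2–3%, excluded share 25–75%, odds ratio 2–3 in that class: overall odds ratios of 1.25–2.5 become 1.00–1.05.

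These values near 1 follow from confining the effect to the removed class. They show what cannot be seen, not how large the bias will be.

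**Power with every case kept.** 12 versus 18 of 400 has about 20% power (two-sided 0.05). Over the odds-ratio range above, power is about 7–77%.

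**Preterm birth, if removed pregnancies leave that analysis too.** Take 6 removals in controls and 12 in the exposed group, the article's preterm rate of 6.2% (24.8 of 400 controls), and an assumed preterm share q of 20–50% among removed cases.

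- Rate among those not removed: r = (24.8 − 6q)/394 = 0.0599 (q = 0.2) or 0.0553 (q = 0.5).
- Exposed group with the same r: (388r + 12q)/400 = 0.0641 or 0.0687.
- Odds ratio against 6.2%: 1.04 or 1.12. After exclusion it is 1.00.

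Table 3 gives a detectable preterm odds ratio of 2.04 at 400 per group.

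**NICU/SCBU admission.** The article gives no admission rate, so no effect size can be derived. Every infant removed under class (a) is a lost event.

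**The case against.** The strongest reply is that the article never says an enrolled woman's birth data are deleted. The neighbouring newborn-screening criterion fits equally well with stopping infant follow-up, and analysis sets are commonly left to the full protocol or SAP. This stands in part. It means that bias in preterm birth and low birth weight cannot be asserted as fact. It does not remove the conflict, because eligibility and outcome list are both stated here and no section reconciles them.

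The malformation outcome is also one of about 20 obstetric secondary outcomes, is not in Table 2, and would have limited power even with every case kept. That stands and limits the weight of the point. Likewise, the article gives no figure for how many diagnoses would fall after enrolment rather than before.

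A reader might infer three stronger things that the document does not support:

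- **That all major malformations are excluded.** The criterion is narrower: immediate NICU need, or a chromosomal abnormality.
- **That the exclusion makes vaping look safer.** The Background's statement on anomaly risk concerns combustible smoking only, and the section on nicotine replacement cites a study finding no increased risk of major malformation. If smoking alone raises anomalies, removal falls mainly on smokers. That would flatter smokers and make vapers look relatively worse against them.
- **That any malformation effect would shrink to nothing.** This holds only if the effect is confined to the excluded class. If all malformations rise equally, the risk ratio is hardly attenuated.

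**Conclusion.** The point holds as a conflict between the Exclusion criteria and the outcome lists. As written, the plan can remove enrolled pregnancies on a post-exposure event that is part of the malformation outcome and of the NICU/SCBU outcome. An exposure effect on the excluded class cannot be seen; effects on other malformations remain visible.

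The size depends on assumed rates and on where an effect would lie: the example runs from 1.50 falling to 1.02, to 2.00 becoming 2.03. The direction of any bias for vaping is open. Any effect on preterm birth or low birth weight depends on an unstated analysis set. For preterm birth, the assumed example hides an odds ratio of at most about 1.12; no figure was worked for low birth weight, where the effect is likely small too. The change should be made because it is cheap and removes selection on an outcome, but the primary conclusions do not turn on it.

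**What to change.** - Limit the abnormality exclusion to abnormalities already known at enrolment.
- Keep every pregnancy diagnosed after enrolment in the malformation, NICU/SCBU, preterm-birth and low-birth-weight analyses.
- Apply the abnormality, metabolic-disorder and cystic-fibrosis exclusions only to the infant wheeze, growth and neurocognitive analyses.
- Report the number excluded by exposure group, at entry and from infant follow-up. Severe cases known before entry will still be missing, and this count lets a reader judge that.

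The cost is one sentence in the eligibility section and an analysis-set flag, with no added participants or visits. Birth outcomes become slightly more heterogeneous, which a sensitivity analysis without these cases can show.

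Restricting the malformation outcome to non-excluded types, and saying so, would also settle the wording. It would leave the severe class unstudied and would not restore the lost NICU events.
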